### Acupuncture Group

After skin disinfection, disposable acupuncture needles (size 0.3 × 40 mm, Xin xinglin brand, manufactured by Beijing Tianyuheng technology company in Beijing, China) will be inserted with the hand. The choice of acupoints refers to the textbook of Chinese acupuncture and moxibustion (31). The body acupuncture points including RN15 (Jiuwei), PC5 (Jianshi), SI3 (Houxi), ST40 (Fenglong). The acupuncture areas of the two groups (AG and SAG) are shown in Figure 2. The locations of the AG and SAG are detailed in Table 2. Acupoints will be stimulated manually (depth of insertion varies from 15 to 30 mm) until patients feel soreness, distension or heaviness (the reaction of “De Qi”). “De Qi” has been shown to be vital for the differential neurophysiological analgesic mechanism between non-responders and responders to acupuncture (32).

**Figure 2 F2:**
[figure not shown]
The acupuncture areas of the acupuncture group and sham acupuncture group.

**Table 2 T2:** Locations of real and sham acupuncture.

**Points**	**Real acupuncture location**	**Sham acupuncture location**
RN15 (Jiuwei)	On the upper abdomen, 1 cun inferior to the xiphisternal junction, on the anterior median line.	1 cm lateral away from the actual points of body acupuncture.
PC5 (Jianshi)	On the anterior aspect of the forearm, between the tendons of the palmaris longus and the flexor carpi radialis, 3 cun proximal to the palmar wrist crease.	
SI3(Houxi)	On the dorsum of the hand, in the depression proximal to the ulnar side of the fifth metacarpophalangeal joint, at the border between the red and white flesh.	
ST40 (Fenglong)	On the anterolateral aspect of the leg, lateral border of the tibialis anterior muscle, 8 cun superior to the prominence of the lateral malleolus.	

### Sham Acupuncture Group

Manipulations of sham acupuncture. The same stainless needles (size 0.3 × 40 mm, described above) will be used. Sham acupuncture in the study is defined as acupuncture with minimal stimulation at the non-meridian and non-acupoint areas (1 cm lateral away from the actual acupoints) and superficial needle insertion (varies from 1 to 3 mm). The number of insertion needles, the time of needle retention, and the frequency of treatment are the same as AG (33, 34).

### Outcome Measures

#### The Primary Outcome

The primary endpoint will be defined as the appearance of a second seizure under treatment or by finishing the 12-month follow-up period without seizures (29, 35).

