## Abstract

**Background:** Acupuncture has been clinically used to treat epilepsy after stroke. However, most of the current clinical studies are observational studies, and there are few well-designed randomized controlled trials (RCTs). Hence, we designed a multicentre RCT to assess the advantages and efficacy of acupuncture for post-stroke epilepsy (PSE).

**Methods/Design:** This is a two-arm, parallel, participants-blinded and assessor-blinded and multicentre RCT. A total of 120 patients with PSE aged from 18 to 75 years will be randomly assigned to two groups (routine treatment plus acupuncture group and routine treatment plus sham acupuncture group) at a 1:1 ratio. The participants will perform acupuncture or sham acupuncture treatment three times a week and be ongoing 8-week treatment. The primary endpoint is the proportion of seizure-free patients. A safety profile will be established. We will record adverse events for the safety evaluation.

**Discussion:** The study will provide high-quality clinical evidence on the effectiveness and safety of acupuncture for treating patients with epilepsy after stroke.

**Clinical Trial Registration:** Chinese Clinical Trial Registry, identifier: ChiCTR2100046114.

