## Methods and Analysis

### Study Design

A multicentre randomized controlled trial (RCT) will be conducted at the Tianjin Nankai Hospital, Tianjin Rehabilitation and Convalescence Center of PLA, Tianjin Gong An Hospital, The Second Hospital Affiliated to Tianjin University of TCM, all of which are teaching hospitals. The protocol was registered with the China Clinical Trial Registry (item number: ChiCTR2100046114), and this study protocol has been approved by the Ethics Committee of Tianjin Gong An Hospital (item number: 2020003). A total of 120 participants will be recruited. All participants will provide written informed consent at the time of recruitment. PSE participants will be recruited and randomly assigned to either conventional therapy plus acupuncture or conventional therapy plus sham acupuncture. The evaluator will evaluate and analyze the results at four points (before treatment, 4 weeks, 8 weeks, and 1 year). Tianjin University of TCM will be responsible for data management and statistics. The flow chart of the trial is illustrated in Figure 1, and Table 1 shows the schedule of measurements.

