**Outcomes**					
The proportion of seizure-free patients			×	×	×
The time recurrence to the first seizure			×	×	×
The proportion of completed diary entries			×	×	×
Mini-mental status examination		×	×	×	×
Montreal cognitive assessment		×	×	×	×
Activities of daily living		×	×	×	×
EEG assessment		×	×	×	×

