### Interventions and Comparison

Both groups will receive routine stroke care and treatment during the whole 8-week study. The program was designed according to the Chinese Stroke Association Stroke Council Guideline will be consistent across groups (27). Chinese herbal medicine will be prohibited during the trial. The routine use of prophylactic anticonvulsant drugs for PSE remains largely controversial. Although many physicians use AEDs as secondary prevention of PSE, there is insufficient evidence on which AEDs are most effective in preventing recurrent epilepsy (1, 4, 5). The 2013 International League Against Epilepsy (ILAE) report suggested carbamazepine (CBZ), Levetiracetam (LEV), phenytoin (PHT) and zonisamide (ZNS) have “level A” evidence (28). Multicenter prospective RCT suggests that LEV in monotherapy is a safe and effective therapeutic option in elderly patients who have suffered PSE (29). So, we will use AEDs to prevent PSE recurrence. AEDs should be tailored to patients according to their age, type of seizure, drug interaction, physical health and other factors. Medication adjustment is handled by neurologists with more than 5 years of clinical experience. If participants present repeated, uncontrolled seizures, they should be given rescue medications that rapidly control the seizure, such as diazepam, midazolam propofol and so on, along with effective supportive treatment, symptomatic treatment, such as keeping the respiratory tract open, correcting acid-base balance, correcting electrolyte disturbances, and preventing or controlling infection (30).

We plan to start acupuncture at the beginning of treatment (together with the AEDs). Acupuncture treatment for the assigned participants will be performed by acupuncturists who have at least 5 years of clinical experience. The participants will receive 30 min of real or sham acupuncture sham acupuncture in a supine position, three times a week for eight weeks. To improve and monitor compliance, those who complete all treatments and assessments will receive financial compensation. Besides, each treatment form and evaluation form will be filled out and signed by patients and investigators.

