#### Secondary Outcomes

Secondary outcomes will include the time recurrence to the first seizure. An event is defined as the time of the first relapse of a seizure after baseline; the time of the seizure is calculated as the difference of weeks between the date of the visit identifying the crisis and the date of the baseline visit. The differences in cognitive functions and quality of life, which will be estimated using the Mini-Mental Status Examination (36), Montreal Cognitive Assessment (37), the Activities of daily living (ADL) (38) and EEG assessment. EEG examinations will be performed at the beginning of the study, during the treatment and follow-up period. Assessments will be conducted by a researcher, who is unaware of the treatment to which the participant is assigned. To evaluate compliance with treatment, the proportion of completed diary entries over the 8-weeks research period will be calculated.

The outcomes will be evaluated at weeks 0, 4, 8, and 12 months. To assess the long-term prognosis, we will follow up with all patients 1 year later through clinic visits, home visits, social media, or telephone contact to collect data on the time and frequency of their occurrence.

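### The primary endpoint joins failure and success with an 'or', does not match the Abstract, and has no time point named as primary

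*Protocol article*

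**What the plan says.** The protocol article describes the primary outcome in three places.

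- **The Primary Outcome section** defines it as "the appearance of a second seizure under treatment or by finishing the 12-month follow-up period without seizures".
- **The Abstract** says: "The primary endpoint is the proportion of seizure-free patients". It gives no time point.
- **Table 1** lists "The proportion of seizure-free patients" among the outcomes and marks it at 4 weeks, 8 weeks and 1 year. The Secondary Outcomes section repeats the schedule ("The outcomes will be evaluated at weeks 0, 4, 8, and 12 months"), as does Study Design. Neither names one time as primary.

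Four other statements affect how the definition can be read.

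- Participant Recruitment enrols patients after a first post-stroke seizure.
- Interventions and Comparison gives acupuncture or sham "three times a week for eight weeks". It also says acupuncture starts together with antiepileptic drugs, and it states no end date for those drugs.
- Secondary Outcomes defines the time-to-event outcome this way: "An event is defined as the time of the first relapse of a seizure after baseline".
- Statistical Analysis assigns the chi-square test to categorical variables in general.

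**The concern.** A primary endpoint has to sort each randomised patient into success or failure, or give a value that can be compared between arms. The sentence in the Primary Outcome section does neither. A patient who relapses and a patient who stays seizure-free for a year both satisfy it. It reads like a rule for ending observation that has been placed where the outcome variable should be.

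The Abstract names a usable kind of variable but not when it is read. Taken together, the passages leave three things open: which seizure counts, whether a seizure after the 8-week course counts, and at which visit the result is judged. If these are settled only once data exist, the main comparison loses its standing as prespecified. The article states a definition that cannot be applied as written, so this is more than detail left to an analysis plan.

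**Working it through.** **Inputs.** From the article: 120 patients, 1:1 (60 per arm), an 8-week course, follow-up to 12 months, assessments at weeks 4 and 8 and at 1 year. The article gives no relapse rate, so I assume 12-month relapse R between 10% and 50%. A two-sided 5% level is also my assumption. There is no stated figure for this endpoint to reproduce.

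**Step 1. Apply the definition under two readings.**

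| Patient | Reading A: second seizure = first relapse; treatment = drugs for 12 months | Reading B: second seizure = first relapse; treatment = 8-week course |
|---|---|---|
| Relapse by week 8 | meets limb 1 | meets limb 1 |
| Relapse between week 8 and month 12 | meets limb 1 | meets neither limb |
| No seizure to month 12 | meets limb 2 | meets limb 2 |

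Under A every completer meets the endpoint, so it is 100% in both arms. Under B late relapsers are not classified. The two faults belong to different readings and do not occur together.

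**Step 2. Size of the unclassified group under B.** With a constant hazard, relapse by week 8 is 1 − (1 − R)^(8/52). The unclassified number is 120 × (R − relapse by week 8).

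- R = 10%: 120 × (0.100 − 0.016) ≈ 10
- R = 20%: 120 × (0.200 − 0.034) ≈ 20
- R = 30%: 120 × (0.300 − 0.053) ≈ 30
- R = 40%: 120 × (0.400 − 0.076) ≈ 39
- R = 50%: 120 × (0.500 − 0.101) ≈ 48

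If relapses come early, the number falls. With a Weibull hazard of shape 0.6 the exponent 8/52 becomes (8/52)^0.6 = 0.325. At R = 40%, relapse by week 8 is 1 − 0.6^0.325 = 0.153, and 120 × (0.400 − 0.153) ≈ 30.

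**Step 3. What three candidate time points could cost.** Simulated null trials (60 per arm, constant hazard, uncorrected chi-square, 100,000 runs per setting), with success declared if any of weeks 4, 8 or 52 gives p < 0.05:

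| 12-month relapse | Single test at 12 months | Any of three tests |
|---|---|---|
| 10% | 0.050 | 0.060 |
| 20% | 0.050 | 0.092 |
| 30% | 0.052 | 0.112 |
| 50% | 0.053 | 0.127 |

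Three independent tests would give 1 − 0.95³ = 0.143. Inflation is small at low relapse rates because few seizures occur by weeks 4 and 8. This table applies only if success may be claimed at any visit.

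**The case against.** The strongest reply is that the intended meaning can be recovered. The Abstract supplies the variable, the Primary Outcome section supplies 12 months, and Statistical Analysis supplies the chi-square test. Seizure-freedom at 12 months was probably meant. That stands as a likely intention and makes the repair small, but the article never states it as the primary variable.

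Four stronger readings are tempting, and the article does not support them.

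- *The primary test is undetermined.* The test family is given. What is unsettled is the variable and the visit it applies to.
- *The primary and secondary outcomes use different events.* Patients enter after a first post-stroke seizure, so the second seizure is plausibly the first relapse, which is the secondary event. The wording differs, but the event need not. For the same reason, leaving out patients with exactly one relapse requires counting from baseline, which the Primary Outcome section does not say.
- *A relapse after week 8 is certainly off treatment.* The article uses the word both for the needle course and for antiepileptic drugs. "Both groups will receive routine stroke care and treatment during the whole 8-week study" points towards 8 weeks, but no stop date for the drugs is given, so the term is ambiguous.
- *The false-positive rate is about 12%.* Nothing in the article says success may be claimed at any visit. Table 1 is a collection schedule, its footnote says so, and the cognitive scales carry the same marks. Handling of multiple time points may sit in an analysis plan not shown here.

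**Conclusion.** The point holds in a limited form. As written, the primary endpoint merges a bad and a good result, cannot be compared between arms, and does not match the Abstract. No time point is named as primary.

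The consequence depends on the reading: no contrast at all under one, unclassified late relapsers under the other. The count of about 10 to 48 of 120 rests on reading treatment as the 8-week course, on an assumed relapse of 10% to 50%, and on a constant hazard. The error rate of about 6% to 13% rests on unadjusted claims at any of three visits. Both are illustrations, not properties of the stated plan. The fault in the definition depends on none of these assumptions.

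**What to change.** Restate the primary endpoint as one yes/no variable at one time point: the proportion of randomised patients with no seizure from baseline to month 12. Any seizure in that window counts as a failure, whether during or after the 8-week course. Then:

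1. State that the 12 months run from baseline, because the present wording does not say where the follow-up period starts.
2. Name the 4-week and 8-week proportions as secondary.
3. Use the same event, the first seizure after baseline, for the time-to-event outcome.
4. Align the Abstract, The Primary Outcome and Secondary Outcomes, and add a note to Table 1 that 1 year is the primary time point. The marks at weeks 4 and 8 can stay.

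The cost is protocol wording only. No extra patients, visits or data are needed, since seizure status to 1 year is already collected.

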#### Secondary Outcomes

Secondary outcomes will include the time recurrence to the first seizure. An event is defined as the time of the first relapse of a seizure after baseline; the time of the seizure is calculated as the difference of weeks between the date of the visit identifying the crisis and the date of the baseline visit. The differences in cognitive functions and quality of life, which will be estimated using the Mini-Mental Status Examination (36), Montreal Cognitive Assessment (37), the Activities of daily living (ADL) (38) and EEG assessment. EEG examinations will be performed at the beginning of the study, during the treatment and follow-up period. Assessments will be conducted by a researcher, who is unaware of the treatment to which the participant is assigned. To evaluate compliance with treatment, the proportion of completed diary entries over the 8-weeks research period will be calculated.

The outcomes will be evaluated at weeks 0, 4, 8, and 12 months. To assess the long-term prognosis, we will follow up with all patients 1 year later through clinic visits, home visits, social media, or telephone contact to collect data on the time and frequency of their occurrence.

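### Time to first seizure is dated by the visit that detects the seizure, so a first relapse after week 8 that is found at the 1-year contact is recorded at about week 52, up to 44 weeks late

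*Protocol article*

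**What the plan says.** The protocol article (Secondary Outcomes) makes the seizure the event: "An event is defined as the time of the first relapse of a seizure after baseline". The time attached to that event, however, is "calculated as the difference of weeks between the date of the visit identifying the crisis and the date of the baseline visit".

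The assessment schedule is given in three places, and they agree:
- Study Design has outcomes evaluated "at four points (before treatment, 4 weeks, 8 weeks, and 1 year").
- Secondary Outcomes says "The outcomes will be evaluated at weeks 0, 4, 8, and 12 months".
- Table 1, in the row "The time recurrence to the first seizure", is marked at 4 weeks, 8 weeks and 1 year only.

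Three other statements bear on the point:
- All patients are followed up at 1 year, in person or remotely, "to collect data on the time and frequency of their occurrence". This is most naturally read as the seizures.
- Treatment is given "three times a week for eight weeks" (Interventions and Comparison).
- The diary appears only as a compliance measure: "the proportion of completed diary entries over the 8-weeks research period will be calculated".

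The article does not say which contacts count as an identifying visit. It gives no expected relapse rate or timing.

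**The concern.** A time-to-event outcome should be timed by the event. Here it is timed by detection, and the scheduled opportunities for detection are very uneven: two in the first 8 weeks, then one at 1 year. A first relapse in week 9 and one in week 51, both found at the 1-year contact, receive the same time. The outcome then cannot show a delay of relapse within weeks 8 to 52, and recorded times to relapse are too long.

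If patients come in between scheduled assessments and those contacts count, the recorded time depends on how soon a patient seeks care. Because the 1-year contact may be by telephone or social media, it is also unclear what the date of the visit would then be.

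This is a rule that the article states, not a detail left to a statistical analysis plan. It also conflicts with the intention, in the same section, to collect when the seizures occurred.

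**Working it through.** The plan has no figure of its own for this outcome, so there is nothing to reproduce. The check has four steps.

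**1. What follows from the text alone.** The last two scheduled assessments are at week 8 and at 1 year (week 52). The gap is 52 − 8 = 44 weeks, or 44/52 = 85% of follow-up. A relapse just after week 8 that is found at 1 year is dated up to 44 weeks late.

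**2. How many relapses this could touch.** Assumptions, none of them from the documents: a 1-year risk R of first relapse, a Weibull time to relapse with shape k (k = 1 is a constant hazard, k < 1 a front-loaded one), and relapses after week 8 detected only at the 1-year contact.

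- F(8) = 1 − (1 − R)^((8/52)^k)
- Share after week 8 = [R − F(8)] / R

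Example with k = 1 and R = 0.50: F(8) = 1 − 0.5^(8/52) = 0.101, so the share is (0.50 − 0.101)/0.50 = 0.798.

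| Shape k | R = 5% | 30% | 50% | 70% | 90% |
|---|---|---|---|---|---|
| 1.0 | 84.3% | 82.2% | 79.8% | 75.8% | 66.9% |
| 0.75 | 75.0% | 72.0% | 68.7% | 63.4% | 52.0% |
| 0.5 | 60.2% | 56.5% | 52.4% | 46.2% | 33.9% |
| 0.35 | 47.4% | 43.6% | 39.5% | 33.6% | 22.5% |

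The share drops below one half when k falls below 0.38, 0.42, 0.47 and 0.55 at R = 10%, 30%, 50% and 70%. With a constant hazard it does so only when R exceeds about 98.8%.

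**3. How far the times move.** Under a constant hazard, relapses in weeks 8 to 52 occur on average at week 29.8 (R = 5%) to week 23.3 (R = 90%). Recording them at week 52 overstates them by 22.2 to 28.7 weeks. Over all four shapes the average overstatement is about 22 to 30 weeks.

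Illustration for the median, with a constant hazard and an assumed R = 40%:
- Weekly hazard λ = −ln(0.6)/52 = 0.00982.
- The true median among relapsers solves F(t) = 0.20, so t = −ln(0.8)/λ = 22.7 weeks.
- The share after week 8 is (0.924 − 0.600)/0.400 = 81%. This exceeds one half, so the recorded median is 52 weeks.

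**4. What it does to a log-rank comparison.** Simulation with 60 patients per arm (120 randomised 1:1), 1,500 runs, constant hazards, an assumed hazard ratio of 0.5, complete follow-up to week 52 and critical value 1.96. Visit-dated times were rounded up to 4, 8 or 52 weeks.

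| Assumed control 1-year risk | Power, seizure-dated | Power, visit-dated |
|---|---|---|
| 50% | 65.2% | 64.2% |
| 30% | 44.5% | 44.4% |

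The Monte Carlo standard error of each figure is about 1.3 points (for example √(0.652 × 0.348/1,500) = 0.012), so neither difference is material.

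**The case against.** The case on the other side has five parts.

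- **Other contacts may detect seizures.** The rule speaks of the visit that identifies the seizure, not of a scheduled outcome visit. Patients attend treatment three times a week for 8 weeks. If those sessions count, relapses up to week 8 are dated to within days. Medication adjustment and rescue treatment may bring further contacts. A reader might infer that the outcome collapses to three possible times (4, 8 and 52 weeks), but the article does not establish that. What stands is that treatment sessions do nothing after week 8, and that the article does not say which contacts count.
- **No share is given.** A reader might infer that most relapses will be recorded at week 52. That needs a relapse pattern which the article does not supply, and it fails when the hazard is steeply front-loaded. This objection stands in full.
- **Relapsers and completers stay distinct.** A reader might think that a relapse dated at week 52 cannot be told from a seizure-free completer. In a time-to-event analysis the first is an event and the second is censored.
- **An exact seizure date is not assured.** What is collected at 1 year may be recall many weeks later. The diary is described only as an 8-week compliance measure, and nothing says that it records seizures or runs to 1 year. It would go too far to say that the right date is already in hand and thrown away.
- **The comparison between arms is little affected.** The same rule and schedule apply to both arms, participants are blinded, and log-rank power hardly moves under proportional hazards. That is correct for a log-rank test. The article itself names only the t-test and the χ2 test. If weeks to relapse were compared as a continuous variable, the distortion would enter the comparison directly.

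**Conclusion.** The rule is wrong as written and should be corrected. It times the relapse by its detection, and no outcome assessment is scheduled for 44 of the 52 weeks. A first relapse after week 8 that is found at the 1-year contact is recorded at about week 52, up to 44 weeks late. This much rests on the text alone.

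How many patients are affected rests on assumptions: about 67% to 84% of first-year relapses under a constant hazard, and about 23% to 47% at Weibull shape 0.35, in both cases if relapses after week 8 are detected only at 1 year.

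The harm is to the reported times, medians and curves, and to any delay of relapse within weeks 8 to 52. A reader might infer that the trial's main conclusion is at risk. The documents do not support that: this is a secondary outcome, and whether a patient is seizure-free at 12 months does not depend on how a seizure is dated. The near-unchanged log-rank power holds for proportional hazards and complete follow-up. It was not tested for effects that mainly shift timing after week 8.

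**What to change.** Replace the dating sentence in Secondary Outcomes with a rule on these lines:

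- Time to first seizure is the date of the first seizure after randomisation, as reported at any contact, minus the date of randomisation. It uses the time of occurrence that the section already plans to collect.
- Seizure-free patients are censored at the last contact at which their seizure status was known.
- Where the seizure date is uncertain, the last seizure-free contact and the detecting contact are recorded as bounds, and the outcome is analysed as interval-censored.

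As any contact counts under this wording, it also removes the doubt about treatment sessions, unscheduled contacts and remote follow-up.

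The cost is a seizure-date field on the case report form, with the two bounding contact dates where needed. Dates first reported at 1 year will carry some recall error, which the interval bounds allow for. The field should be in place as early as possible, because dates not recorded at the contact may be hard to recover later.
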